**Fig. 1 Fig1:**
[figure not shown]
Overview of the PGP-COS development study

### Scope

This PGP-COS and corresponding outcome measurement instruments is aimed at monitoring the progress of PGP in both research (randomised and non-randomised studies) and clinical practice. The target population is women with PGP during pregnancy or postpartum (defined as any time after a birth), as this is by far the most common presentation. Very little is known about other, smaller groups with PGP due to a lack of research; subsequently this COS focuses on PGP in pregnant and postpartum women. We hope that as further literature emerges concerning other PGP groups, we will be able to expand or adapt this COS for these groups in future studies, where appropriate. PGP is defined as pain between the posterior iliac crest and the inferior gluteal fold, particularly in the vicinity of the sacroiliac joints, that may radiate in the posterior thigh and can occur in conjunction with or separately in the symphysis pubis [3]. However, we will exclude pain of the pelvic girdle attributable to specific pathologies such as inflammatory arthropathies, infection, and trauma.

### Phase one: Generating the list of potential outcomes

#### Systematic search of the literature

We will conduct a systematic review of the literature to identify outcomes measured in intervention studies and systematic reviews related to PGP. We chose to limit the review to these study types as our PGP-COS will be developed for effectiveness trials, and follows COMET’s mission. We will search the following databases from inception: PubMed, the Cochrane Library, PEDro and Embase. Two reviewers will independently select relevant records by title/abstract and full-text, using the selection criteria outlined in Table 1. Disagreement will be resolved through discussion or if necessary by involving a third reviewer. Health, clinical, social and economic outcomes (and their verbatim definitions) will be extracted and their corresponding outcome measurement instruments, where reported, will be recorded. The quality of outcome reporting will be assessed using the six questions proposed by Harman et al. [16]. Subsequently we will group the outcomes into outcome domains using the OMERACT Filter 2.0 framework [17], but all identified outcomes will be presented for rating in the Delphi survey.

**Table 1 Tab1:** Selection criteria for the systematic review of outcomes used in the existing PGP literature

Population	Women with PGP during or after pregnancy. PGP is defined as pain between the posterior iliac crest and the inferior gluteal fold, particularly in the vicinity of the sacroiliac joints, that may radiate in the posterior thigh and can occur in conjunction with or separately in the symphysis pubis [3]. We will exclude studies that include women with PGP and low back pain without differentiation between the two. We will also exclude studies that examine a population with PGP resulting from specific pathologies (e.g. infection, spondyloarthropaties, trauma).
Intervention	Any intervention aimed to treat/prevent PGP
Comparator	Any comparator intervention or control
Outcome	Any outcome measured to assess/monitor PGP
Study design	Intervention studies (randomised or non-randomised), systematic reviews of interventions

#### Interviews with patients

We will conduct semi-structured interviews using open-ended questions with a purposive sample of approximately 15 pregnant/postpartum women with PGP (5 in Ireland, 5 in Sweden, 5 in Mexico), because those experiencing PGP directly, might indicate different outcomes of importance than those measured by clinicians/researchers in studies [18]. Participants must be aged 18 years or more and have PGP (as primary complaint) at the time of the interview. PGP is defined as pain between the posterior iliac crest and the inferior gluteal fold and/or at the symphysis pubis [3], and confirmed by a qualified clinician following a physical examination. A pragmatic approach will be used in that the clinician will identify patients with PGP at his/her discretion based on current guidelines [3]. Following a complete history, the examination will include PGP pain provocation tests and functional tests, in particular, but not exclusively, the posterior pelvic pain provocation (P4) test and the functional active straight leg raise (ASLR) test [19–22], which have been shown to have high sensitivity and specificity. In addition, other body areas that might be the source of a patient complaint will be examined to rule out other diagnoses. Participants must also be able to fluently speak and understand the local language (English, Spanish, or Swedish). Interviews will be transcribed and analysed using thematic analysis.

#### Methodological study 1: A systematic review with or without patient interviews to identify potential outcomes

When examining existing COS development studies, some authors include patient interviews in establishing the initial list of potential outcomes but others only search the literature [23]. Current guidance recommends that potential relevant outcomes are identified from several sources: systematic reviews of published studies, reviews of qualitative work, examination of items collected in national audit data sets, and interviews/focus groups with key stakeholders [14]. However, no studies have examined the impact of including patient interviews compared to conducting a systematic review only to identify the initial list of potential outcomes, on the final COS. Including interviews with participants presents additional costs and workload to the COS development team, including additional ethics applications, time and resources. It may be that the inclusion of patient representatives in the Delphi survey and in the consensus meeting makes patient interviews at the outcome identification stage redundant, but this is unknown. We will assess how the outcomes that are derived from the interviews only (if any) are rated in each round of the survey, and how many/type (if any) are subsequently included in the final PGP-COS. We will also examine the extent to which additional outcomes provided by patient representatives in round 1 of the Delphi survey overlap with the outcomes obtained from the interviews.

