**Methods:**

The PGP-COS study will include five phases: (1) A systematic review of the literature and semi-structured interviews with 15 patients (three countries) to form the initial list of outcomes for the Delphi survey; (2) A 3-round Delphi including patients, clinicians, researchers and service providers; (3) A systematic review of methods for measuring the outcomes in the preliminary PGP-COS identified in the Delphi survey; (4) A face-to-face consensus meeting to agree on the final PGP-COS and methods for measuring the COS; (5) Global dissemination.

To address the methodological questions, we will assess the number and type of outcomes, in the final PGP-COS, that were exclusively derived from the interviews. Secondly, we will randomise Delphi survey participants to either a 5-point or 9-point importance rating scale, and examine potential differences in ‘important’ ratings between the groups.

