## Objectives

To collate a list of reported outcomes from a systematic review of the literature of studies on PGP and from patient interviews for use in a Delphi survey;To develop consensus on a preliminary PGP-COS, using the list of outcomes from Objective 1, via a 3-round international electronic Delphi survey;To synthesise the evidence on the available outcome measurement instruments for measuring the construct outcomes (e.g. pain) in the preliminary PGP-COS;Using the preliminary PGP-COS (Objective 2), develop a final PGP-COS for use in all future studies on PGP, and in clinical practice, including how to measure the outcomes in the COS, via an international face-to-face consensus meeting with key stakeholders;To disseminate and promote the implementation of the COS to key stakeholders internationally;

In addition, we have two methodological objectives:6.To determine if including patient interviews in addition to a systematic review to identify the initial list of outcomes influences the final COS;7.To evaluate any differences in using a 9-point versus a 5-point rating scale in the Delphi survey, in terms of its impact on the number of ‘important’ ratings received for each outcome in each round of the survey and on the final PGP-COS.

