#### Participants

We will invite people from all stakeholder groups, aiming for approximately 40 experts from each stakeholder group (patients, clinicians, researchers, service providers/policy makers) to participate (which will provide 20 people randomised to each scale; see methodological study 2). We will recruit participants for the Delphi survey through professional organisations, electronic discussion lists, and patient organisations. We will also encourage snowball sampling, asking participants to forward the invitation appropriately.

Eligible participants will be: (a) Researchers who are actively involved in research related to PGP/lumbopelvic pain and have at least one peer-reviewed publication on the topic; (b) Clinicians, currently treating patients with PGP (including chiropractors, physiotherapists, osteopaths, orthopaedic surgeons etc.); (c) Patients with PGP; (d) Policy-makers, involved in formulating policies related to the management of musculoskeletal conditions including PGP; and (e) Service providers of services for musculoskeletal conditions including PGP. Participants must be able to read and understand English in order to participate.

#### Round 1

Round 1 will collect demographic data including nationality, age, gender, stakeholder group and profession. Participants will rate the importance of each listed outcome. Outcomes will be rated in each round on a 9-point scale [16] or on a 5-point scale (see methodological study 2 below). Participants will also be given the opportunity to add any additional outcomes not already in the list that they think are important. All outcomes from round 1 will be forwarded to round 2.

#### Round 2

Participants who responded to round 1 will be presented with feedback (descriptive statistics) on their own and others’ scores from round 1 and asked to rescore all outcomes and score new outcomes added in round 1. The reason for providing feedback from the previous round to participants is to increase the degree of consensus [14]. Participants will rate outcomes using the same scale they used in round 1. Outcomes from round 2 will be forwarded to round 3 where 70% or more of participants score the outcome as ‘important’ (7 or more on the 9-point scale, or 4 or more on the 5-point scale), and less than 15% of participants scoring an outcome as ‘not important’ (3 or less on the 9-point scale, or 2 or less on the 5-point scale) (Tables 2 and 3).

**Table 2 Tab2:** The 9-point rating scale

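### Methodological study 1: the overlap between patients' round 1 additions and the interview outcomes is near zero by construction, so it cannot show whether Delphi patients make the interviews redundant

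*Protocol article*

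**What the plan says.** Four statements in the protocol article bear on this point.

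- **Where the list comes from.** The abstract (Methods) uses a systematic review and "semi-structured interviews with 15 patients (three countries) to form the initial list of outcomes for the Delphi survey". Objective 1 collates outcomes "from a systematic review of the literature of studies on PGP and from patient interviews for use in a Delphi survey", and Objective 2 runs the Delphi "using the list of outcomes from Objective 1".
- **Interview outcomes are rated from round 1.** Methodological study 1 states: "We will assess how the outcomes that are derived from the interviews only (if any) are rated in each round of the survey". It will also count how many of these outcomes, and of what type, reach the final core outcome set (COS).
- **What may be added.** Under Phase two, Round 1, participants can "add any additional outcomes not already in the list that they think are important".
- **The overlap check.** Methodological study 1 will also look at how far "additional outcomes provided by patient representatives in round 1 of the Delphi survey overlap with the outcomes obtained from the interviews".

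The same section says it is unknown whether having patients in the Delphi and at the consensus meeting makes interviews at the identification stage unnecessary. It notes that interviews bring extra cost, workload and ethics applications.

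**The concern.** The overlap check is the only planned analysis that appears to address whether Delphi patients would bring up the interview outcomes themselves. For that purpose, high overlap would have to be possible when patients would have raised those outcomes, and low overlap when they would not. The survey layout removes the first possibility, because the outcomes in question are shown to patients before they are asked what is missing.

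What is at stake is a methodological conclusion. The section says that no study has yet examined the effect of adding interviews to a systematic review. A low overlap reported without explanation could be taken by later COS teams as evidence that patients in a Delphi do not supply what interviews find. That result would have been fixed before any data were collected.

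**Working it through.** The plan gives no figure for this analysis, so there is none to reproduce. The check is one of set logic on the protocol's own statements.

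**Definitions**

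- R = outcomes from the systematic review.
- I = outcomes from the interviews (k of them).
- L = the list shown in round 1.
- A = outcomes that patients add in round 1.

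**Step 1: content of the list.** The abstract and Objectives 1 and 2 give L = R ∪ I. Methodological study 1 confirms this independently: interview-only outcomes cannot be rated in every round unless they are listed in round 1. The systematic-search section adds that "all identified outcomes will be presented for rating in the Delphi survey". That sentence concerns the literature search, and the argument does not depend on it.

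**Step 2: what may be added.** The Round 1 rule restricts A to outcomes outside L.

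**Step 3: the overlap.** Since I lies inside L and A lies outside L, A ∩ I is empty.

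**Step 4: dependence on the truth.** Let p be the probability that an interview outcome would have been volunteered by patients had it not been listed. The quantity of interest is k × p. The quantity measured under the rules is k × p × 0 = 0:

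| True p | Interview outcomes patients would have supplied | Overlap under the stated rules |
|---|---|---|
| 0% | 0 of k | 0 of k |
| 50% | 0.5k of k | 0 of k |
| 100% | k of k | 0 of k |

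The values of p are illustrative. The number of patients (about 40 planned) does not enter, so a larger panel would not help.

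**Step 5: is there a group with a different list?** None is described. The randomisation in Methodological study 2 concerns only the 9-point or 5-point scale. Nobody is described as seeing the review outcomes alone.

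**Step 6: how the overlap could exceed zero.** Interviews are analysed thematically, and the article gives no rule for wording items or matching them. Three routes remain:

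- a patient enters a listed outcome again in other words;
- a patient splits a listed outcome more finely;
- interview content was merged into a broader item, and a patient names the part that was lost.

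All three depend on how the list was worded and how answers are matched. None measures what patients would have offered without the interviews.

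**The case against.** The strongest reply accepts the logic and disputes the consequences. Most of it stands.

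- **A reader might infer that objective 6 cannot be answered.** The document does not support that. Objective 6 asks whether adding interviews influences the final COS. Methodological study 1 has two direct measures of this: ratings of interview-only outcomes by round, and their number and type in the final COS. The abstract mentions only the number and type in the final COS, and the overlap check is introduced as an extra. Both main measures can be computed as planned. They show whether interview outcomes survive once listed, not whether patients would have raised them, so they do not replace the overlap check, but objective 6 does not rest on it.
- **A reader might infer a certain bias in favour of interviews.** The article sets no threshold or interpretation rule for the overlap. A low value could also be read as Delphi patients contributing outcomes that the 15 interviews missed. The misreading in favour of interviews is likely but not certain. What can be said firmly is that the measure is uninformative about redundancy.
- **Redundancy is background, not an objective.** It is raised as a possibility and also involves the consensus meeting. The text does not say outright that the overlap check tests it, although the placement of the check suggests so.
- **An open question before the list is not the ideal comparison.** In a review-only Delphi, patients would see the review list and then add what is missing. Unprompted recall may miss outcomes they would add at that stage, and so understate redundancy. This is correct and limits how the replacement result may be read.

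One further reply does not stand: that a fuller protocol or analysis plan may deal with the matter. The stated list, the stated rule for additions and the stated measure together fix the result. Further analysis detail cannot recover answers that the survey does not invite.

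**Conclusion.** The point holds for the overlap check alone. Followed as written, the check gives an overlap near zero whatever patients would have volunteered, and any overlap that does appear reflects wording and matching. It cannot inform whether including patients in the Delphi makes interviews redundant.

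This conclusion assumes that interview outcomes are carried onto the round 1 list, as the Objectives and Methodological study 1 indicate, and that all participants see the same outcomes, since no alternative list is described.

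The severity is moderate. This is a secondary, descriptive analysis within an embedded methodological study. The consensus rules and the selection of core outcomes do not depend on it.

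**What to change.** Before the outcome list is shown in round 1, add one open question on which outcomes matter most to the participant, then lock the page.

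- Ask it of all stakeholder groups, so that round 1 is the same for everyone.
- Code patients' answers against the interview-only outcomes, with a matching rule written beforehand.
- Report the proportion of interview-only outcomes reproduced unprompted, with a confidence interval. Its width cannot be given now, because k is unknown until the interviews are analysed.
- Describe the result as a likely lower bound on what patients would add after seeing a review-only list.
- Keep the existing box for additions after the list, but use it only to complete the list.

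At minimum, drop the overlap analysis or state that it cannot support any conclusion on redundancy.

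The cost is one extra survey page and the coding of short free text, with no additional participants. The question may prime later ratings slightly. Both randomised scale arms would receive it, so that effect should be equal between them. The change must be made before round 1 opens, because unprompted answers cannot be obtained once patients have seen the list.

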### Phase two: Online international Delphi survey

A sequential 3-round electronic, international Delphi study will be conducted including key stakeholders (patients/public, healthcare professionals, researchers, and service providers) to produce a preliminary PGP-COS. We will use online SurveyMonkey software to conduct the survey (www.surveymonkey.com). Each round will remain open for 14 days and a reminder email will be sent out four working days before closure. The data from each round will be analysed and presented to participants in the subsequent round. We will assess attrition rates for each round for all stakeholder groups.

#### Participants

We will invite people from all stakeholder groups, aiming for approximately 40 experts from each stakeholder group (patients, clinicians, researchers, service providers/policy makers) to participate (which will provide 20 people randomised to each scale; see methodological study 2). We will recruit participants for the Delphi survey through professional organisations, electronic discussion lists, and patient organisations. We will also encourage snowball sampling, asking participants to forward the invitation appropriately.

Eligible participants will be: (a) Researchers who are actively involved in research related to PGP/lumbopelvic pain and have at least one peer-reviewed publication on the topic; (b) Clinicians, currently treating patients with PGP (including chiropractors, physiotherapists, osteopaths, orthopaedic surgeons etc.); (c) Patients with PGP; (d) Policy-makers, involved in formulating policies related to the management of musculoskeletal conditions including PGP; and (e) Service providers of services for musculoskeletal conditions including PGP. Participants must be able to read and understand English in order to participate.

#### Round 1

Round 1 will collect demographic data including nationality, age, gender, stakeholder group and profession. Participants will rate the importance of each listed outcome. Outcomes will be rated in each round on a 9-point scale [16] or on a 5-point scale (see methodological study 2 below). Participants will also be given the opportunity to add any additional outcomes not already in the list that they think are important. All outcomes from round 1 will be forwarded to round 2.

#### Round 2

Participants who responded to round 1 will be presented with feedback (descriptive statistics) on their own and others’ scores from round 1 and asked to rescore all outcomes and score new outcomes added in round 1. The reason for providing feedback from the previous round to participants is to increase the degree of consensus [14]. Participants will rate outcomes using the same scale they used in round 1. Outcomes from round 2 will be forwarded to round 3 where 70% or more of participants score the outcome as ‘important’ (7 or more on the 9-point scale, or 4 or more on the 5-point scale), and less than 15% of participants scoring an outcome as ‘not important’ (3 or less on the 9-point scale, or 2 or less on the 5-point scale) (Tables 2 and 3).

**Table 2 Tab2:** The 9-point rating scale

	9-point scale								
Outcome	Not important			Unsure of importance			Important		
Pain	1	2	3	4	5	6	7	8	9
	○	○	○	○	○	○	○	○	○

**Table 3 Tab3:** The 5-point rating scale

	5-point scale				
Outcome	Not important		Unsure of importance	Important	
Pain	1	2	3	4	5
	○	○	○	○	○

#### Round 3

Round 3 will further prioritise outcomes by rescoring the outcomes based on round 2 feedback. Only participants who completed round 2 will be invited to round 3. Outcomes scored by 70% or more of participants as ‘important’ (7 or more on the 9-point scale, or as 4 or more on the 5-point scale), and less than 15% of participants scoring an outcome as ‘not important’ (3 or less on the 9-point scale, or 2 or less on the 5-point scale) will be included in the preliminary PGP-COS. At the end of the round 3 survey we will also include a question to ask if they would be willing to take part in the face-to-face consensus meeting.

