## Background

Low back pain is a leading cause of Years Lived with Disability (YLD) [1], is the sixth largest contributor to Disability Adjusted Life Years (DALYs) [2] and is associated with high costs of healthcare utilisation and absenteeism from work. Pelvic Girdle Pain (PGP) has sometimes been considered one of the main subgroups of low back pain; however, currently experts agree that PGP has distinct symptomatology and that differentiation between low back pain from lumbar origin and PGP is essential for appropriate management [3]. Moreover, PGP may include symphysis pubis pain, which cannot be classified as low back pain. Subsequently, PGP is a distinct condition, and treatment, examination and outcomes should be studied taking this into account to increase our understanding of PGP.

Pelvic Girdle Pain can be related to blunt or repetitive trauma, osteoarthritis or arthritis, and can as such affect both men and women. In most cases there is no clear explanation for the onset of PGP, but it is particularly common during pregnancy and most studies have been conducted on pregnant or postpartum women. Very little is known about other PGP groups due to a lack of studies. Pelvic Girdle Pain affects around half to two thirds of women at some point during pregnancy [4, 5] and 8.5% continue to have significant symptoms two years postpartum [6]. It is also the number one cause of sick leave during pregnancy [7–9] with large economic, social and psychological impact on individual families and the wider society. There is an urgent need for effective preventative and management strategies to address this personal and societal burden for women in fertile age [3, 10]. However, emerging studies measure a variety of outcomes and measure the same outcomes by different methods [5, 10], rendering synthesis and translation to clinical practice difficult and sometimes impossible.

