#### Participants

A purposive sample of approximately 20 experts will form the consensus panel. The following stakeholder groups will be included: (a) Researchers who are actively involved in research related to PGP and have at least one peer-reviewed publication on the topic*;* (b) Clinicians currently treating patients with PGP (including chiropractors, physiotherapists, osteopaths, orthopaedic surgeons etc.); (c) Women (pregnant/postpartum) with PGP; (d) Policy-makers and service providers involved in formulating policies/providing services related to the management of musculoskeletal conditions, including PGP. The meeting will be held in English and translators may be required.

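### The Delphi admits any patient with PGP, although the core outcome set is meant for pregnant and postpartum women

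*Protocol article*

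**What the plan says.** The Scope section sets the population: "The target population is women with PGP during pregnancy or postpartum (defined as any time after a birth". It then narrows by cause: "However, we will exclude pain of the pelvic girdle attributable to specific pathologies such as inflammatory arthropathies, infection, and trauma". Other PGP groups are deferred, with the hope to "expand or adapt this COS for these groups in future studies".

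Under Phase two, Participants, the Delphi eligibility list runs from (a) to (e). The patient entry is "c) Patients with PGP", and the only further condition is being able to read and understand English. Recruitment goes through professional and patient organisations and discussion lists, with snowball forwarding. On data collected, the article says: "Round 1 will collect demographic data including nationality, age, gender, stakeholder group and profession".

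The equivalent entry for the consensus panel under Phase four is "c) Women (pregnant/postpartum) with PGP". Table 1 (the review of outcomes) and the interview section also name women during or after pregnancy.

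**The concern.** The Delphi vote forms the preliminary core outcome set, and it is the one stage whose patient criterion omits the population limit. The term PGP does not supply that limit. The Background section says: "Pelvic Girdle Pain can be related to blunt or repetitive trauma, osteoarthritis or arthritis, and can as such affect both men and women". Read literally, the Delphi list would admit a man with pain after trauma.

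Three things are at stake.

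- **Votes.** An outcome that fails the 70%/15% rule in round 2 does not go to round 3. No route is stated by which the consensus meeting could restore it.
- **Added outcomes.** Participants may propose outcomes in round 1, and these are scored in round 2. Out-of-scope patients could therefore enlarge the list as well as vote on it.
- **Methodological study 1.** It examines how far outcomes added by Delphi patients overlap with those from the interviews. If the two patient groups follow different entry rules, a lack of overlap may reflect different populations and not the value of interviewing.

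**Working it through.** **Step 1: compare the criteria.**

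| Section | Limited to pregnant/postpartum women? | Specific pathologies excluded? |
|---|---|---|
| Scope | Yes | Yes |
| Table 1, review of outcomes | Yes | Yes |
| Interviews with patients | Yes | Not listed, but a clinician confirms PGP and rules out other diagnoses |
| Phase two, Delphi participants | No | No |
| Phase four, consensus panel | Yes | Not restated |

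The Delphi entry is the only one without the pregnancy/postpartum limit. On cause it differs from the Scope and Table 1, but not from the consensus panel entry.

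**Step 2: inputs for the size of the effect.**

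- Planned panel: about 40 in each of 4 stakeholder groups, so 4 × 40 = 160 (Phase two, Participants; Sample size).
- Rule: at least 70% of participants rate the outcome important and fewer than 15% rate it not important (Rounds 2 and 3). No separate threshold for patients is given, so the rule is taken over the pooled panel.
- Assumption, not in the document: k = 10 of the 160 voters are out of scope. Full response is also assumed.

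**Step 3: the pooled shift.** Let p be the share rating the outcome important among in-scope voters and q the share among out-of-scope voters.

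Pooled share = [(160 − k)p + kq]/160, so the shift from p is (k/160)(q − p). With k = 10 this is 0.0625 × (q − p).

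**Step 4: worst cases at k = 10.** The pooled rule needs 0.70 × 160 = 112 important ratings. The 150 in-scope voters alone would need 0.70 × 150 = 105.

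- None of the 10 rates it important: all 112 must come from 150, and 112/150 = 74.7%. Outcomes from 70.0% to just under 74.7% in scope (105 to 111 ratings) are dropped.
- All 10 rate it important: 112 − 10 = 102 suffice, and 102/150 = 68.0%. Outcomes with 102 to 104 in-scope ratings are kept although they fall short of 70% in scope.
- All 10 rate it not important: the outcome fails at 0.15 × 160 = 24 such ratings, so 14 in-scope ratings are enough (14/150 = 9.3%). Among the 150 alone, 22 such ratings would still pass (22/150 = 14.7%).

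**Step 5: a less extreme case.** Let p = 75% and q = 40%. Pooled: (150 × 0.75 + 10 × 0.40)/160 = 116.5/160 = 72.8%, and the outcome stays. Even with q = 0 it is 112.5/160 = 70.3%, and it stays.

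**Step 6: range over the assumed k.** The upper limit is 112/(160 − k) and the lower limit is (112 − k)/(160 − k).

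| k | In-scope share needed if none of the k rates it important | In-scope share sufficient if all k do |
|---|---|---|
| 5 | 112/155 = 72.3% | 107/155 = 69.0% |
| 10 | 112/150 = 74.7% | 102/150 = 68.0% |
| 20 | 112/140 = 80.0% | 92/140 = 65.7% |

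**The case against.** The best defence is that the Scope governs the whole project. It defines PGP and names the population, and Phase three refers back to it for the target population. On that view the Delphi entry is shorthand. This has some force for the excluded causes, since the consensus panel entry does not restate them either. It is weaker for pregnancy and postpartum status. The Scope's definition of PGP is anatomical and carries neither sex nor pregnancy status, and the other patient-facing sections state that limit for themselves.

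A second defence is that wrongly kept outcomes must still win 70% at the consensus meeting, including at least one patient representative's vote, from a panel whose patients are pregnant or postpartum women. That stands, and it leaves wrongly dropped outcomes as the main exposure. It is also true that about 120 of the 160 planned voters are not patients. They vote in other capacities, however, and the patient group is there to speak for the target population.

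Several stronger readings are tempting but unsupported:

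- **That every patient who is not pregnant is out of scope.** The Scope counts any time after a birth as postpartum, so only people who are neither pregnant nor postpartum fall outside.
- **That out-of-scope voters could never be identified.** The demographic list is introduced as non-exhaustive and includes gender, so men could be found. A status or cause question is not mentioned, which does not show that none exists.
- **That an outcome is lost once support among patients falls below 70%.** With 10 of 40 patients out of scope at 40% and the rest at 75%, the patient figure is (30 × 0.75 + 10 × 0.40)/40 = 66%. The protocol has no patient-only threshold, and the pooled figure in Step 5 stays above 70%.

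**Conclusion.** The point holds as an inconsistency in a stated criterion. The article gives the Delphi eligibility list in full, so this is not an omission due to condensing, and the patient entry is wider than the population the set is meant to serve. The gap is clear for people who are neither pregnant nor postpartum and only possible for excluded causes.

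The effect on the preliminary set is confined to outcomes near a threshold. The band given for k = 10 is a worst case. It rests on an assumed count, full response, pooled counting and unanimous out-of-scope votes. The document shows that such voters may enter. It does not show that they are wanted or how many would come. The correction is worth making because it is cheap before launch and hard to make once votes are cast.

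**What to change.** 1. Reword entry (c) of the Delphi list to follow the Scope: women with PGP during pregnancy or at any time after a birth, not attributable to a specific pathology.
2. Add one or two screening items to round 1 on pregnancy/postpartum status and any known cause of the pain.
3. State that, within the patient group, only in-scope patients count toward the 70%/15% rules. The other stakeholder groups count as planned.

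The cost is one sentence, one or two survey questions, and a slightly smaller patient pool to recruit from.
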